### Primary outcome

The primary outcome will measure the incidence of the major cardiovascular and cerebrovascular adverse events (MACCE). MACCE is defined when the following conditions occur during maintenance HD: (1) Occurrence or deterioration of congestive heart failure and myocardial infarction; (2) Cardiogenic shock and/or sudden cardiac death; (3) Transient ischemic attack or occurrence and deterioration of Cerebral infarction and cerebral hemorrhage; (4) Pulmonary embolism and peripheral arterial thrombosis or embolism [16].

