### Secondary outcomes

The secondary outcomes include:

(1)All-cause mortality at 1year, 2 years and 3 years follow-ups.(2)The incidence of intradialytic hypotension (IDH). According to the National Kidney Foundation Kidney Disease Outcomes Quality Initiative (KDOQI), IDH is defined as “a decrease in systolic blood pressure (SBP) by ≥ 20 mmHg or a decrease in mean arterial pressure (MAP) by ≥10 mmHg, accompanied by hypotension symptoms such as abdominal discomfort, yawning, sighing, nausea, vomiting muscle cramps, restlessness, dizziness or fainting, and anxiety” [17]. In addition, we will compile the proportion of patients with an absolute nadir systolic BP < 90 mmHg (pre-dialysis systolic BP < 160 mmHg) or a nadir BP < 100 mmHg (pre-dialysis BP ≥ 160 mmHg) during HD, as it most potently associated with mortality [18].(3)The incidence of hypoglycemia. A serum glucose level below 3.9 mmol/L (70 mg/dl) is defined as hypoglycemia [19,20]. In addition, three levels of hypoglycemia will be classified according to the American Diabetes Association [21, 22]. Level 1 hypoglycemia: a serum glucose concentration <3.9 mmol/L) but ≥3.0 mmol/L, regardless of hypoglycemia symptoms, including but are not limited to, shakiness, irritability, confusion, tachycardia, sweating, and hunger. Level 2 hypoglycemia: a serum glucose concentration <3.0 mmol/L. Level 3 hypoglycemia: a severe hypoglycemia event (altered mental and/or physical functioning) that requires assistance from another person for recovery, irrespective of glucose level.(4)Blood pressure variability during HD. Systolic blood pressure (SBP) and diastolic blood pressure (DBP) will be measured before HD, every hour during HD, and after HD. Blood pressure coefficient of variation (CVBP) will be used to represent the variability of SBP and DBP during HD. CVBP = standard deviation of blood pressure/ mean blood pressure.(5)Blood glucose variability during HD. Within the first 48 weeks after enrollment, we will measure blood glucose (postprandial blood glucose) during the first HD process each week (0h before HD, 2h during HD and 0h after HD). Blood glucose coefficient of variation (CVBG) = standard deviation of blood glucose/ mean blood glucose.(6)Dysfunction of vascular access.(7)Cardiac function. Left ventricular end diastolic diameter (LVEDD), left ventricular posterior wall thickness (PWTd), interventricular septal thickness (SWTd), and left ventricular ejection fraction (LVEF) will be measured using echocardiography. Meanwhile, we will also calculate relative wall thickness (RWT), left ventricular mass (LVM), and left ventricular mass index (LVMI).(8)Fatigue level: ICFS-10 fatigue rating scale and the 9-item Fatigue Severity Scale (FSS) [23].

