### Sample size determination

Sample size calculation was performed based on the primary outcome MACCE. Our hypothesis posits that the risk of MACCE in the glucose-containing dialysate group will decrease by 25% compared to the glucose-free dialysate group. The Log-rank test was used to compare the primary outcome between groups. We anticipate completing the enrollment within 1 year, and followed by a 3-year follow-up period. We performed sample size calculations with PASS 15.0.5 utilizing an α value of 0.05 and a power of 90%. Accordingly, we require a total of 544 participants (272 per group). Taking into account a potential 10% dropout rate, we determined that 600 participants should be enrolled in this study.

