### Statistical analysis

Continuous variables will be expressed as mean ± standard deviation (SD) when normally distributed with homogeneous variance; otherwise, median with interquartile range (IQR) will be reported. Categorical variables will be displayed as numbers and percentages. Baseline characteristics between the two groups will be compared using a two-sample t-test or Pearson’s χ2 test. Linear mixed effects models will be utilized for the analysis of repeated measurement data to estimate the adjusted mean change between the groups from baseline to each follow-up period. Baseline level, time, and treatment will serve as fixed effects, with patients as a random covariate to account for repeated measurements. Results will be reported with 95% confidence intervals (CI). The cumulative probability of MACCE will be compared between groups using Kaplan-Meier curves and log-rank test. Ultrafiltration rate (UFR), along with other clinically relevant factors such as patient characteristics (including age, gender and comorbidities), vascular access and anticoagulation will be indeed included as covariates in the multivariate models for the primary outcome. DKD and the frequency of HDF as preplanned subgroup stratification factors. P-value less than 0.05 denoted statistical significance, and we will use SAS 9.4 (SAS Institute Inc, Cary, North Carolina) and SPSS 23.0 (IBM, USA) for all analyses.

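### Kaplan-Meier is the named estimator of cumulative MACCE probability, but deaths outside the MACCE definition can only be censored, so it overstates MACCE incidence in each arm

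*Protocol article*

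**What the plan says.** All references are to section 2, Methods and analysis, of the protocol article.

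- **Statistical analysis** fixes both the quantity and the method: "The cumulative probability of MACCE will be compared between groups using Kaplan-Meier curves", together with a log-rank test.
- **Primary outcome** calls that quantity an incidence: "The primary outcome will measure the incidence of the major cardiovascular and cerebrovascular adverse events (MACCE". The only death named among the components is in item 2: "Cardiogenic shock and/or sudden cardiac death". A death from another cause enters the endpoint only if a listed event, such as myocardial infarction or stroke, led to it or came before it.
- **Secondary outcomes** keeps death in general apart from MACCE: "All-cause mortality at 1year, 2 years and 3 years follow-ups".
- **Sample size determination** states the hypothesis on the risk of MACCE ("the risk of MACCE in the glucose-containing dialysate group will decrease by 25% compared to the glucose-free dialysate group") and sets the horizon: "We anticipate completing the enrollment within 1 year, and followed by a 3-year follow-up period".

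The article does not mention competing events or a cumulative incidence function, and gives no rule for deaths outside MACCE. It states no expected MACCE rate and no mortality rate.

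**The concern.** A patient who dies of infection or cancer, say, without a MACCE can no longer have one. With MACCE as the event, the Kaplan-Meier method has one place for that patient: censored at death. Censoring assumes that the patient would have gone on to have MACCE at the same rate as those still followed. The complement of the curve then estimates the MACCE risk in a hypothetical setting without other deaths. That is neither the incidence named in the Primary outcome section nor the cumulative probability named in the Statistical analysis section.

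At stake are the absolute figures that readers will take from the primary display: the 3-year MACCE risk in each arm and whatever is derived from it. The abstract says that the results are meant to inform dialysate selection, and absolute risks are part of that.

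**Working it through.** **Plan's own figure.** There is none to reproduce, since the article states no MACCE risk for either arm. The sample size of 544 does not bear on this point.

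**Direction, without outside figures.** Let λ(t) be the MACCE hazard among patients alive and free of MACCE, S_M(t) the Kaplan-Meier survival function with MACCE as the only event, and S_D(t) the corresponding function for non-MACCE death.

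- 1 − KM = ∫ S_M(t) λ(t) dt
- Cumulative incidence = ∫ S_M(t) S_D(t) λ(t) dt

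Because S_D(t) ≤ 1, one minus Kaplan-Meier is never below the cumulative incidence. It is strictly above once non-MACCE deaths occur among patients still at risk and MACCE events follow.

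**Size, under assumed rates.** Take a constant MACCE hazard l, a constant non-MACCE death hazard d, and the 3-year horizon from Sample size determination:

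- 1 − KM = 1 − exp(−3l)
- Cumulative incidence = l/(l+d) × [1 − exp(−3(l+d))]

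For l = 0.20 and d = 0.10:

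- 1 − exp(−0.60) = 1 − 0.5488 = 45.12%
- (0.20/0.30) × [1 − exp(−0.90)] = 0.6667 × (1 − 0.4066) = 39.56%

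| l per year | d per year | 1 − KM (%) | Cumulative incidence (%) | Overstatement (points) |
|---|---|---|---|---|
| 0.15 | 0.05 | 36.24 | 33.84 | 2.4 |
| 0.20 | 0.10 | 45.12 | 39.56 | 5.6 |
| 0.25 | 0.12 | 52.76 | 45.30 | 7.5 |
| 0.15 | 0.02 | 36.24 | 35.25 | 1.0 |
| 0.25 | 0.02 | 52.76 | 51.40 | 1.4 |

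The last two rows show the lower end: at 2 non-MACCE deaths per 100 patient-years the error is about 1.0 to 1.4 points.

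**Between arms.** Read the hypothesised 25% reduction as a hazard ratio of 0.75 (the article does not state the scale). Then l is 0.20 in the glucose-free arm and 0.15 in the glucose-containing arm. Let d = 0.10 in both.

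| | Glucose-free (%) | Glucose-containing (%) | Difference (points) | Ratio | 1/difference |
|---|---|---|---|---|---|
| 1 − KM | 45.12 | 36.24 | 8.9 | 0.803 | 11.3 |
| Cumulative incidence | 39.56 | 31.66 | 7.9 | 0.800 | 12.7 |

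The risk difference is overstated by about 1 point, the ratio barely changes, and a number needed to treat would come out slightly too low.

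**The case against.** The strongest reply is that the primary inference is untouched. The log-rank test compares cause-specific MACCE hazards and is valid with non-MACCE deaths censored. This stands: a reader might infer that the primary test is biased or its type I error inflated, and nothing in the article supports that. The between-arm shift is also much smaller than the error within an arm, and the article does not itself plan a 3-year MACCE risk difference or a number needed to treat. Both stand, and they limit the point to the reported absolute probabilities.

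Second, the article quantifies no mortality. It excludes patients over 75, those with a life expectancy under 1 year, and those with active infection or under cancer treatment. The MACCE definition is broad, and deaths after a first MACCE do not compete. A reader might assume a large bias because these are dialysis patients, but the article gives no rate to support that. This affects the size, not the direction.

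Third, a reader might fear that a harmful effect on other deaths would go unseen. The MACCE curves would not show it, but all-cause mortality at 1, 2 and 3 years is a secondary outcome and a data monitoring committee meets every three months.

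Fourth, this is a condensed article, and handling of deaths may be set out in the full protocol or analysis plan. That would excuse silence. Here, however, the article names an estimator and a quantity, and the one does not estimate the other.

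**Conclusion.** The point holds for the estimation of absolute MACCE risk. One minus Kaplan-Meier overstates the named quantity in each arm. The direction follows from the method and the endpoint definition alone. The size rests on assumed constant hazards: 2.4 to 7.5 points at 3 years over the main range, and about 1.0 to 1.4 points if non-MACCE death is as low as 0.02 per year. The overstatement of the risk difference, about 1 point in the example, further assumes a hazard ratio of 0.75 and equal non-MACCE death in both arms. If the dialysate altered non-MACCE death, the error would differ by arm, and the article offers no basis for putting a figure on that.

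The phrase about events during maintenance HD in the Primary outcome section might be read as making transplantation a second competing event. The article does not mention transplantation, and the phrase can be read in more than one way, so the point rests on deaths alone.

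This should be corrected, but it does not threaten the primary test or the estimated relative effect.

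**What to change.** In the Statistical analysis section:

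1. Replace the Kaplan-Meier curves for MACCE with Aalen-Johansen cumulative incidence curves by arm, with death outside the MACCE definition as a competing event.
2. Take any reported 3-year MACCE risks and their difference, with a 95% confidence interval, from these curves.
3. Keep the planned log-rank test and describe it as a comparison of cause-specific hazards.
4. Add one supporting analysis of time to MACCE or death from any cause, whichever comes first.

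The cost is a few lines of plan text and a little extra code in SAS, which is already the planned software. Deaths are already collected for the mortality outcome, and separating sudden cardiac death from other deaths is already needed for the primary endpoint. The design and sample size do not change. The only other consequence is that the reported absolute risks will be slightly lower.

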### Monitoring and quality control

To ensure the quality and regulatory compliance of the trial, we will establish an independent data monitoring committee (DMC). The DMC will comprise five members who possess expertise in fields such as nephrology, dialysis management, dialysis nursing, trial methodology and biostatistics. And DMC chair is [name] from West China Hospital, Sichuan University. The DMC meeting will be held every three months, and we will create a procedural document for the meetings, and strictly follow the document.

### Study status

This study is currently recruiting participants. After the registration completed, we have recruited the first participant on October 20, 2024. And recruitment is expected to be completed in December 2025. Data collection and results presentation will be completed after 3-year of follow-up.

### Ethics and dissemination

All participants will provide the written informed consent, which states that participation is voluntary and can be terminated at any time. Individual data will be securely stored, password-protected, and accessible only by the research team. The results of this trial will be presented at national as well as international scientific conferences. And the final manuscript will be published in a peer-reviewed journal.

## 3. Discussion

This trial is a prospective, open-label, multicenter RCT aimed at evaluating both the efficacy and safety of 5.5 mmol/L glucose-containing dialysate for maintenance HD patients. Asymptomatic hypoglycemia occurs in approximately 40% HD patients using glucose-free dialysate [24]. Blood glucose can be dialyzed out through the dialysis membrane as it is a small molecule. Additionally, a considerable number of ESKD patients experience obvious gastrointestinal symptoms that may reduce their food intake, leading to malnutrition and a tendency towards hypoglycemia before dialysis. Blood glucose loss during HD, malnutrition and tight glycemic control all contribute to the occurrence of hypoglycemia in HD patients [25–27]. Hypoglycemia can result in fundus hemorrhage, angina, anemia, and even coma and death, which indeed increase mortality of ESKD patients [3]. Therefore, preventing the occurrence of hypoglycemia in dialysis patients is an urgent issue.

Several studies had reported the benefits of glucose-containing dialysate in reducing incidence of hypoglycemia and improving heart rate variability in maintenance HD patients [8–10,28]. However, these studies were all observational with small sample sizes, and there is still no definitive evidence on the long-term prognosis of maintenance HD patients using glucose-containing dialysate. Furthermore, there are ongoing controversies regarding the benefits of glucose-containing dialysate, as several studies have not identified it as a superior choice for all maintenance HD patients [6,14]. Glucose-containing dialysate may stimulate oxidative stress, induce hypertriglyceridemia and less effective in potassium removal during HD [6].

To the best of our knowledge, this study will be the first RCT not only focusing on the incidence of hypoglycemia and hypotension during dialysis, but also on the long-term prognosis, especially the incidence of MACCE, in maintenance HD patients using glucose-containing dialysate compared to glucose-free dialysate. Hypoglycemia may lead to sympathetic nerve activation and the release of a large amount of catecholamines, which may cause hemodynamic changes and have a significant impact on the cardiovascular system, such as myocardial ischemia or heart failure [29]. Therefore, it is crucial to pay attention to the incidence of MACCE in HD patients, which we have identified as the primary outcome of this trial. We aim for the results of this trial to support the improvement of optimal dialysis treatment prescriptions and guidelines for ESKD patients.

However, there are still several limitations to this study. Firstly, due to the nature of the intervention and practical constraints, blinding of patients and clinicians is not feasible in this study. Nevertheless, we will meticulously design our methods for recruitment, randomization, allocation, outcomes assessment, data collection, and analysis to minimize bias. Secondly, the majority of hospitals participating in this study are located in southwestern China, which implies that the results of this trial should be interpreted with caution regarding region and ethnicity. In the future, larger, national and international multicenter RCTs will be needed to comparatively evaluate the efficacy and safety of glucose-containing dialysate versus glucose-free dialysate.

In summary, we will conduct a prospective, multicenter RCT to assess the efficacy and safety of 5.5 mmol/L glucose-containing dialysate for maintenance HD patients. And we will establish several working committees to ensure high-quality conduct of this trial and employ rigorous methods to minimize bias in participant recruitment, randomization, allocation, outcome assessment, data collection, and analysis. Our aspiration is that this trial will provide valuable insights for future dialysate selection and the enhancement of dialysis treatment prescriptions.
